#### 2.3.8. Criteria for discontinuation of study.

Trial discontinuation is defined as stopping the entire trial midway through a clinical trial that has not been completed according to the protocol. The trial shall be discontinued if one of the following occurs.

(1) Serious safety issues arise during the trial.(2) In the course of the trial, it is found that the clinical trial protocol has a major error, evaluating the drug effect is difficult, or serious deviations in the implementation render it difficult to continue to evaluate the efficacy of the drug.(3) Administrative authorities withdraw the trial for other causes and need to clarify the reasons.

### 2.4. Sample size

Taking α = 0.05 and β = 0.15, a 2-sided test will be used. The estimated sample incidence of P_1_ = 25% for the test group and P_2_ = 43% for the control group will be brought into the following equation:

$$\begin{array}{l} n_{1}=n_{2}=1641.6\times {\left(\frac{u_{\alpha }+u_{2\beta }}{sin^{-1}\sqrt{P_{1}}-sin^{-1}\sqrt{P_{2}}}\right)}^{2} \end{array}$$

### 2.5. Randomization and blinding

The randomization scheme provided by the Department of Statistics, Guangzhou University of Traditional Chinese Medicine. A stratified randomization method will be used. Statistical analysis system software will be applied to generate a randomized allocation of the treatments received by the patients, that is, the treatment assignments corresponding to the running numbers 001 to 300 will be listed, and the study subjects will be randomly divided into 2 groups: the test group and the control group.

The study will have a double-blind design with placebo as the control, and the number of cases in the test and control groups will be 1:1, which will be a secondary blinding done by the Statistics Department of Guangzhou University of Traditional Chinese Medicine. The trial drug and placebo will be provided by Guangdong Zhongsheng Pharmaceutical Co., Ltd. and packaged according to the random assignment and blinding methods. The blind codes will be sealed in duplicate and separately stored in the drug clinical trial institution and the sponsoring unit in charge of this study.

### 2.6. Interventions

The basic treatment will involve following the guideline-guided drug regimen for post-PCI AMI and HF.

Refer to China Society of Cardiology of Chinese Medical Association 2015 Guideline on the diagnosis and therapy of ST-segment elevation MI, 2016 Guideline on the diagnosis and therapy of non-ST segment elevation acute coronary syndrome, and 2016 ESC Guidelines for the Diagnosis and Treatment of Acute and Chronic HF. Drug therapy will be selected based on the severity of the patient’s condition and indications. The indications, doses, and courses of treatment will be strictly formulated according to the guideline recommendations: Dual-anti platelet-therapy, statins, ACEI/angiotensin receptor blockers, β-blockers, anti-ischemic therapy drugs, etc. Those with acute HF after infarction will be treated according to the situation: diuretics, vasodilators, positive inotropic drugs, etc; those with stable acute HF or chronic HF with diuretics, ACEI/angiotensin receptor blockers, β-blockers, aldosterone receptor antagonists, anti-HF treatment drugs, etc.

Test group: basic treatment + CXSTC, 3 capsules/dose, 3 times a day with warm water.

Control group: Basic treatment + placebo, 3 capsules/time, 3 times a day, with warm water.

Duration of treatment: 3 months.

Follow-up: 6 months.

Combined medications: Except for the medications prescribed for the course of the study, the use of TCM (proprietary Chinese medicine, tonics, injections) will be prohibited for all patients; for drugs or other treatments that must be continued for preexisting comorbidities and their symptoms (other than the symptoms of the disease), the name, usage, dosage, and duration of the drug (or other treatment) shall be recorded in detail; in case of comorbidities or symptoms during the study period, all symptomatic treatments will be administered according to clinical routine, and the name, usage, dosage, and time of the drug (or other therapy) shall be recorded in detail; and combined medications and therapies that need to be used during the study in case of adverse events shall be recorded in detail in the case report form.

### 2.7. Outcomes

#### 2.7.1. Efficacy indicators

(1) The main efficacy indicator will be the incidence of HF. The incidence of HF was recorded on days 3, 7, 14, 1 month, and 3 months after drug administration, and after discontinuation of the drug until 3 months.(2) Secondary efficacy indicators

① Cardiac function classification: before treatment and after drug administration on days 3, 7, 14, 1 month, and 3 months and after discontinuation of the drug until the 3rd month of the examination record.

② Cardiac ultrasound: the examination records shall be recorded before treatment and on days 7 and 3 months after drug administration.

③ Six-minute walk test score: recorded on days 7, 14, 1 month, and 3 months after drug administration.

④ TCM syndrome score: recorded before treatment and on days 7, 14, 1 month, and 3 months after drug administration. The efficacy = (the integral value before treatment − the integral value after treatment)/ the integral value before treatment × 100%); It is assessed at 4 levels: clinical recovery: clinical symptoms or syndrome score decreased by ≥95% from the baseline; marked efficacy: the syndrome score decreased by ≥70% and <95%; efficacy: the syndrome score was a decrease of at least 30% and <70%; invalid: the syndrome score was a decrease of <30%; and worsen: the syndrome score exceeded the baseline after treatment.

⑤ Quality of survival score (the Minnesota living with heart failure questionnaire): recorded before treatment and on days 14, 1 month, and 3 months after drug administration.

⑥ Brain natriuretic peptide level was recorded before treatment and on days 3, 7, 14, and 3 months after drug administration.

⑦ Ultrasensitive C-reactive protein level: recorded before treatment and on days 3, 7, 14, and 3 months after drug administration.

Total efficacy rate = (clinical recovery + marked efficacy + efficacy) cases/a total number of cases × 100%.

#### 2.7.2. Safety indicators.

Routine blood, urine, stool, liver and kidney function, electrolyte monitoring, cardiac enzymology, and electrocardiogram.

#### 2.7.3. Adverse events.

Although adverse effect of CXSTC has not been observed, possible adverse reactions should be concerned, including gastrointestinal reactions, gastrointestinal bleeding, and skin allergy. Any adverse events occurred should be recorded in “Adverse events form” and the treatment process and results also need to be recorded in detail.

#### 2.7.4. Collection of biological specimens.

The patient’s blood, urine and stool samples will be collected before and after intervention, and clearly marked according to the unified format. Then, the samples will be transferred in frozen pipe and stored at −80°C for preservation in the biological sample bank of the First Affiliated Hospital of Guangzhou University of Chinese Medicine. Consents and other documents like the collection and usage of participant data and biological specimens could be inquired from the registry web or the corresponding author.

### 2.8. Study quality control

A multi-center study coordinating committee shall be established, and the study leaders and sponsors of each participating unit shall be the coordinating committee members. The coordinating committee will be responsible for the implementation of the trial and the resolution of trial-related issues. The sponsor commissions the company to be the contract research organization for the trial. The contract research organization shall identify monitors with medical/pharmacological backgrounds and good clinical practice training to supervise the whole process of the clinical trial. In the event of an adverse event or reaction in a clinical trial, the investigator may take necessary measures to protect the safety of the patient according to the condition, record the event, and decide whether to terminate the trial. If a serious adverse event occurs, the clinical trial shall be withdrawn and appropriate treatment measures taken for the patient immediately. Additionally, the same shall be reported to the State Food and Drug Administration department within 24 hours of drug registration, the department of safety supervision and the local provincial drug regulatory administration, sponsor, and the ethics committee. The sponsor shall immediately inform other trial centers and investigators involved in this trial and ensure that all reporting procedures required by laws and regulations are met.

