## Abstract

**Methods::**

This will be a multi-center, randomized, double-blind, placebo-parallel controlled trial. A total of 300 patients diagnosed with AMI and undergoing percutaneous coronary intervention within 12 hours of diagnosis will be randomized 1:1 into 2 groups: the control group that will be administered conventional Western medicine plus placebo and the trial group that will be administered XST along with the conventional Western medicine. The duration of treatment will be 3 months and the follow-up will be up to 6 months for both groups. The main efficacy indicator is the incidence of HF. The secondary efficacy indicators are cardiac function classification, 6-minute walk test score, TCM syndrome score, survival quality score, brain natriuretic peptide level, ultrasensitive C-reactive protein level, and cardiac ultrasound result. Data will be collected to analyze the underlying mechanisms by using IBM SPSS 23.0 software.

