#### 2.3.7. Additional exclusion criteria.

(1) Patients who do not cooperate with randomization, do not take any trial drug after randomization, or use very little drug (<10%).(2) Patients who use the prohibited combinations of treatments or drugs, which would affect the effectiveness and safety determination.(3) No data after randomization.

The case will be judged for exclusion after a discussion between the principal investigator, data manager, statistical analysis expert, and sponsor during a blinded review.

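### Section 2.8 makes withdrawal from the trial compulsory after a serious adverse event: read literally this contradicts section 2.3.8, and read as patient withdrawal it may stop heart failure being recorded

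*Protocol article*

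**What the plan says.** The rule is in section 2.8 (Study quality control) of the protocol article: "If a serious adverse event occurs, the clinical trial shall be withdrawn and appropriate treatment measures taken for the patient immediately". The sentence just before it deals with adverse events in general and is discretionary. The investigator may act to protect the patient, "record the event, and decide whether to terminate the trial". After the reporting duties, the section adds that "The sponsor shall immediately inform other trial centers and investigators involved in this trial".

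Stopping the whole trial has its own section, 2.3.8: "Trial discontinuation is defined as stopping the entire trial midway through a clinical trial that has not been completed according to the protocol". The grounds listed there are serious safety issues, a major protocol error or deviations that prevent evaluation of the drug, and withdrawal by the authorities. A single serious adverse event is not among them.

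The primary endpoint is the incidence of HF (section 2.7.1), recorded at visits from day 3 to month 3 "and after discontinuation of the drug until 3 months". Section 2.6 gives 3 months of treatment and "Follow-up: 6 months", and the abstract says "the follow-up will be up to 6 months for both groups".

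**The concern.** Section 2.8 is an instruction that nine centres have to apply, and neither way of reading it gives a sound rule.

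Read literally, the first serious adverse event stops the trial. In patients treated by PCI for acute infarction such an event is foreseeable, so this can hardly be meant.

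Read as patient withdrawal, it obliges the site to take the patient out of the trial, not merely off the capsule. Stopping treatment and ending observation are different decisions, and the sentence does not separate them. A patient with a reinfarction or a bleed in the first weeks could leave the trial before any later HF is recorded. Such patients may well be at higher risk of HF than the rest, so the loss need not be random. At stake is the completeness of the primary endpoint: some power if the loss is equal in the two arms, and a biased comparison if it is not.

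**Working it through.** **1. The text side by side.**

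| Place | Trigger | Action | Force |
|---|---|---|---|
| 2.8, preceding sentence | adverse event or reaction | investigator decides whether to terminate | discretionary |
| 2.8, the rule | a serious adverse event | the trial is withdrawn; the patient is treated | compulsory |
| 2.3.8 | serious safety issues, major protocol error or deviations, authorities | the entire trial stops | compulsory, but on listed grounds |

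The literal reading conflicts with the third row. Two features favour the patient-level reading: the same sentence goes on to treatment of the patient, and the sponsor's next step is to inform the other centres, not to close them. On that reading the rule still conflicts with the discretion in the first row, and what is withdrawn is participation in the trial, not study drug.

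**2. Inputs for an illustration of size.** From section 2.4: two-sided alpha 0.05, beta 0.15 (planned power 85%), HF 25% in the test group and 43% in the control group. From the abstract: 300 patients randomised 1:1, so 150 per arm. The documents give no rate of serious adverse events, so the loss rate L is an assumption, taken as equal in both arms.

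**3. The plan's own formula.** The arcsine roots are 30.00 and 40.98 degrees, a difference of 10.98.

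n per arm = 1641.6 × ((1.960 + 1.036)/10.98)² ≈ 122.3, so 123 per arm or 246 in total.

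The 300 stated is larger. The article does not explain the difference, and this point does not depend on it.

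**4. Power at 150 per arm** (pooled two-proportion test).

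Power = Φ[(|p1 − p2| − 1.96 × SE0)/SE1]

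- SE0 = √(2 × 0.34 × 0.66/150) = 0.0547
- SE1 = √(0.25 × 0.75/150 + 0.43 × 0.57/150) = 0.0537
- (0.18 − 1.96 × 0.0547)/0.0537 = 1.355, so power = 0.912

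**5. Power with loss.** *Dropped* means n = 150(1 − L) per arm with rates unchanged. *Counted HF-free* means n = 150 with both rates multiplied by (1 − L).

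| Assumed loss | Dropped: n per arm | Power | Counted HF-free: rates | Power |
|---|---|---|---|---|
| 0% | 150 | 0.912 | 25.0% v 43.0% | 0.912 |
| 5% | 142.5 | 0.898 | 23.8% v 40.9% | 0.890 |
| 10% | 135 | 0.882 | 22.5% v 38.7% | 0.865 |
| 20% | 120 | 0.842 | 20.0% v 34.4% | 0.803 |

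Power reaches 0.85 at a loss of 18.1% (dropped) or 12.6% (counted HF-free).

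**6. What the HF-free column assumes.** It supposes that no lost patient had HF recorded before the serious event or as that event, so it is a worst case for a given equal loss. If half of the HF in these patients had already been recorded (again an assumption), the multiplier becomes (1 − L/2). Power is then 0.890 at 10% loss and 0.865 at 20%, and reaches 0.85 only near 25%. Counting lost patients as HF-free also shrinks the risk difference when loss is equal: at 10% it falls from 18.0 to 38.7 − 22.5 = 16.2 percentage points.

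**The case against.** The strongest reply is that the harm is inferred. Section 2.8 is a safety paragraph in a condensed article, and its wording may be a translation slip. It does not say that HF visits stop, and the follow-up statements in the abstract and section 2.6 make no exception for patients who stop early. The full protocol may well provide for follow-up after withdrawal. This limits the point: loss of HF data is a possible consequence of the rule, not a stated one. It does not remove it, because the complaint is about a compulsory rule that the article states and that fits neither section 2.3.8 nor the sentence before it. The follow-up statements set the schedule but do not say that a withdrawn patient remains on it.

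Three stronger readings are tempting and are not supported:

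- **That the trial would really close at the first serious event.** The rest of the sentence and the sponsor's duty to inform other centres point to the individual patient.
- **That section 2.7.1 shortens observation for early stoppers**, because it dates the last HF record from the end of drug. With 3 months of treatment and 6 months of follow-up, that phrase most naturally describes months 3 to 6 of the schedule. It does not discuss early stopping.
- **That section 2.3.7 would exclude these patients from analysis** through its criterion for those who "do not take any trial drug after randomization, or use very little drug (<10"%). That section does not list serious adverse events and leaves exclusion to a blinded review. Converting the threshold into days needs an assumed denominator. It is a separate matter.

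It is also fair to say that the power loss is small at moderate loss rates, and that enrolment is limited to Killip class I patients with ejection fraction above 50% and no previous chronic HF or old infarction.

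**Conclusion.** The point holds as a minor fault in a stated rule. The sentence in section 2.8 is wrong on either reading: literally it contradicts section 2.3.8, and as patient withdrawal it compels removal from the trial where stopping study drug at the investigator's discretion would do. Under the second reading, HF after a non-HF serious event could go unrecorded before month 6. HF that is itself the serious event, or that precedes it, is not affected.

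The size of any loss is unknown because no event rate is given. With assumed equal loss, the design has room: 10% loss leaves 88% power, or 86% at worst, and the planned 85% is breached only beyond about 18% or 13%. Bias from unequal or informative withdrawal would matter more than power, but nothing in the documents allows it to be estimated or shows that it would occur.

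**What to change.** Reword section 2.8 to say three things:

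- A serious adverse event may lead to stopping study drug for that patient, at the investigator's discretion.
- The whole trial stops only on the grounds in section 2.3.8.
- Every randomised patient is followed for HF to month 6 from the start of treatment, whether or not study drug was stopped, unless consent is withdrawn.

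The cost is a change of wording and keeping the already scheduled visits for patients who stop the drug early. No patients are added.

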### 2.9. Statistical analysis plan

All data will be statistically analyzed using SPSS 23.0 software. The measurement data will be expressed as mean ± standard deviation to test the normality of the samples. If the distribution is normal and the variances are homogeneous, the *t* test shall be used. The rank sum test will be used if the distribution is not normal or the variances are not equal. Count data will be expressed as percentages and tested by the χ^2^ test or Fisher method. Rank data will be tested by rank sum test; the Cox regression model will be used to observe the relationship between the risk of occurrence of endpoint events and each influencing factor. A 2-sided *P* value < .05 will be set as the significant level.

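### Continuous secondary outcomes are compared by a pre-tested t test or rank-sum test with no baseline adjustment, which gives up precision; unequal variances are sent to the wrong test

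*Protocol article*

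**What the plan says.** Section 2.9 of the protocol article fixes one rule for measurement data. They are summarised as mean and standard deviation, and normality is checked. The t test applies if the data are normal with homogeneous variances. Otherwise, "The rank sum test will be used if the distribution is not normal or the variances are not equal". Cox regression is named, but only for endpoint events. No method named for continuous data takes a baseline covariate.

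Section 2.7.1 records pre-treatment values for cardiac ultrasound, the TCM syndrome score, the Minnesota questionnaire, BNP and ultrasensitive CRP. For example: "Brain natriuretic peptide level was recorded before treatment and on days 3, 7, 14, and 3 months after drug administration". The six-minute walk test has follow-up visits only. Neither section says whether the t or rank-sum test is run on follow-up values or on changes.

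For TCM efficacy, section 2.7.1 grades the percent reduction from baseline: "It is assessed at 4 levels". It then lists five grades, the last being "worsen: the syndrome score exceeded the baseline after treatment".

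**The concern.** Three features of the rule deserve attention, and all three are written down rather than left to a fuller plan.

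- **Baseline.** A measurement taken before treatment usually predicts the later one. A two-sample test on follow-up values ignores that information. A test on changes uses it with a fixed slope of one, which is generally not the best slope.
- **Unequal variances.** When means are the reported summary, unequal spread is a reason to use Welch's test. The rank-sum test addresses a different hypothesis, so a reported mean difference could sit beside a P value that does not test it.
- **Pre-test.** The test is chosen from the data it will analyse. With two to four follow-up visits per outcome, one outcome could get a t test at one visit and a rank-sum test at the next.

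The TCM grades raise a smaller matter. Section 2.9 sends ranked data to a rank-sum test, which needs each patient to have one rank. A patient whose score rises above baseline is graded as worsened. That patient also has a decrease below 30%, and so meets the definition of invalid.

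**Working it through.** **Inputs from the document.** Total 300 ("A total of 300 patients diagnosed with AMI and undergoing percutaneous coronary intervention within 12 hours of diagnosis will be randomized 1:1 into 2 groups"), hence 150 per arm, and a two-sided 5% level (section 2.9). The sample size in section 2.4 concerns heart-failure incidence only. The plan gives no power figure for any continuous outcome, so there is none to reproduce.

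**Assumed input.** The correlation r between baseline and follow-up is not in the document. I show 0.3, 0.5 and 0.7.

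**Power.** Take an effect that an unadjusted test on follow-up values detects with 70% power. With z(0.975) = 1.960 and z(0.70) = 0.524, the sum is 2.484. At 150 per arm this is a standardised difference of 2.484 × √(2/150) = 0.287. If an analysis multiplies the residual SD by k, then

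power = Φ(2.484/k − 1.960),

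with k = 1 for follow-up values, √(2 − 2r) for changes and √(1 − r²) for ANCOVA.

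| r | k, change | Power, change | k, ANCOVA | Power, ANCOVA | Per arm for ANCOVA to match 150 unadjusted, 150(1 − r²) |
|---|---|---|---|---|---|
| 0.3 | 1.183 | Φ(0.140) = 56% | 0.954 | Φ(0.644) = 74% | 137 |
| 0.5 | 1.000 | Φ(0.524) = 70% | 0.866 | Φ(0.909) = 82% | 113 |
| 0.7 | 0.775 | Φ(1.247) = 89% | 0.714 | Φ(1.519) = 94% | 77 |

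ANCOVA is ahead of both alternatives in every row. Against follow-up values the gain grows with r. Against changes it is largest at low r and narrows to 89% versus 94% at r = 0.7.

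**Unequal variances.** Simulation with normal data, equal means and 150 per arm (5,000 runs, Monte Carlo error about 0.3 points):

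| SD ratio | Rank-sum rejects | Welch rejects |
|---|---|---|
| 1.5 | 5.3% | 5.3% |
| 2 | 6.0% | 5.4% |
| 3 | 7.0% | 5.3% |

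A separate run of 2,000 gave 6.8% and 7.3% for the rank-sum test at ratios 2 and 3. The drift is real but modest.

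**Which outcomes.** Section 2.7.1 lists seven secondary indicators. Cardiac function class is ordinal, and the walk test has no baseline. Five remain with a recorded baseline: ultrasound, TCM score, Minnesota score, BNP and CRP. The TCM grading already uses baseline through the percent reduction, which leaves four for which no use of baseline is described.

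**TCM grades.** Recovery, marked efficacy, efficacy, invalid and worsened make five. The total efficacy rate counts the first three only, so the overlap between the last two cannot change it. It matters only where the grades are ranked.

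**The case against.** The strongest reply is that this is a condensed article. Covariates, the contrast visit and a repeated-measures model normally belong in a statistical analysis plan, and their absence here is no error. That is right as far as it goes. But the article does state a rule, and the rule as stated has no baseline term and sends unequal variances to the rank-sum test. The point concerns that stated rule.

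Other parts of the reply stand:

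- **Validity.** An unadjusted comparison of randomised arms is valid; adjustment is a gain in efficiency.
- **Size of the gain.** It rests on an assumed correlation. Baselines are taken around an acute infarction and PCI, so the correlation with month 3 may be low. At r = 0.1, 70% power on follow-up values becomes only 70.4%.
- **False positives.** A reader might infer that the pre-test, or the rank-sum test, inflates false positives when the capsule does nothing. The evidence does not support that. With identical arms, simulating the whole two-stage rule (10,000 runs, 150 per arm) gave 5.2%, 4.7% and 5.0% rejection for normal, lognormal and gamma data. The 6–7% figure needs equal means with a two- to threefold difference in SD between randomised arms, and nothing in the document suggests one.
- **Skewed data.** With lognormal data of equal arithmetic mean and log-SDs of 0.7 versus 1.0, the rank-sum test rejects in 71% of trials. This is not a fault peculiar to that test: a Welch test on the logs rejects in 73%. Both answer a question other than equality of arithmetic means, and for skewed biomarkers that may be a legitimate question if it is stated.

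**Conclusion.** The point holds as one of efficiency and of matching the test to the reported summary, confined to secondary outcomes. The heart-failure incidence comparison and its sample size are untouched.

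- **Baseline.** The loss against ANCOVA at r of 0.3 to 0.7 is about 4 to 24 percentage points of power if follow-up values are tested (70% against 74–94%). It is about 18 down to 5 points if changes are tested (56–89% against the same 74–94%). These figures assume the correlation, a 70% starting power and 150 analysed per arm.
- **Unequal variances.** The rank-sum test is the wrong remedy when means are reported. The consequence for its level is small with normal data and absent when the arms share one distribution.
- **Breadth.** It would be too broad to say that nearly every secondary outcome loses power, or that no baseline is used anywhere: the ordinal class, the walk test and the TCM percent reduction are exceptions.
- **TCM grades.** The count and the overlap are a genuine but minor wording error, separate from the rest.

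The change should be made because it is free, not because the planned tests are invalid.

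**What to change.** 1. Remove the normality and variance pre-test as the rule for choosing a test.
2. Analyse each continuous outcome with a recorded baseline by ANCOVA or a repeated-measures mixed model (arm, visit, arm by visit). Include the baseline value and the randomisation stratum, and name month 3 as the contrast.
3. Log-transform BNP and CRP, and state that the comparison is then of geometric means.
4. For the walk test, adjust for stratum only and use a standard error that allows unequal variances.
5. Analyse the TCM score as a score. Keep the grades as five mutually exclusive classes, with invalid meaning a decrease of 0 to under 30% and worsened meaning above baseline, and correct the stated number of levels.

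The cost is wording in the analysis plan, settled before unblinding. No new data, visits or patients are needed, and SPSS 23 fits these models.

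### The apparent primary comparison of HF incidence is valid but unadjusted, so it forgoes a modest gain in precision from natriuretic peptide and ultrasound values already recorded at baseline.

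*Protocol article*

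**What the plan says.** Section 2.7.1 makes the incidence of HF the main efficacy indicator. Section 2.4 sizes the trial as a comparison of two proportions: "The estimated sample incidence of P_1_ = 25% for the test group and P_2_ = 43% for the control group". Section 2.9 assigns tests by type of data, and its only between-group test for count data is this: "Count data will be expressed as percentages and tested by the χ^2^ test or Fisher method". It names no covariate for that test, and it does not name a test for the main endpoint as such.

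Two baseline measurements are available. For natriuretic peptide, section 2.7.1 says: "Brain natriuretic peptide level was recorded before treatment and on days 3, 7, 14, and 3 months after drug administration". For cardiac ultrasound it says: "the examination records shall be recorded before treatment and on days 7 and 3 months after drug administration".

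The one regression in the plan is also in section 2.9: "the Cox regression model will be used to observe the relationship between the risk of occurrence of endpoint events and each influencing factor". Its covariates are not listed, and its place relative to the chi-square or Fisher test is not given.

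**The concern.** HF incidence is a proportion and was sized as one, so the reader will take the chi-square or Fisher test as the main treatment comparison. If baseline BNP and ejection fraction predict HF after infarction, a test that ignores them leaves explainable variation in the error term. The confidence interval is then wider, and power lower, than the same patients could give. That baseline values predict HF is an assumption, because the article reports no association between them and the outcome. The Discussion (section 3) names the small number of cases as a limitation, so precision that costs no extra patients deserves a look.

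**Working it through.** **Inputs from the documents**
- Two-sided α = 0.05 and β = 0.15 (section 2.4), so u_α = 1.960 and u_2β = 1.036.
- HF incidence of 25% (test) and 43% (control) (section 2.4).
- 300 patients allocated 1:1 (Abstract and section 2.5), so 150 per group.

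**Step 1: the plan's own formula.** The constant 1641.6 works with angles in degrees.
- arcsin √0.43 = 40.98° and arcsin √0.25 = 30.00°, a difference of 10.98°.
- n = 1641.6 × ((1.960 + 1.036)/10.98)² = 122.3, so 123 per group (246 in total).

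The article prints 300 without the formula's result. The gap would fit an allowance of 18%, since 246/(1 − 0.18) = 300, but no allowance is stated. Both sizes are carried forward: 150 is the planned number, and 123 is what the formula needs.

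**Step 2: power of the unadjusted test.** Power = Φ(√(n/1641.6) × 10.98 − 1.960).
- n = 123: Φ(3.004 − 1.960) = 85.2%.
- n = 150: Φ(3.318 − 1.960) = 91.3%.

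**Step 3: power with adjustment.** If baseline values explain a share R² of the outcome variance, the variance of the comparison shrinks by about 1 − R². Then power = Φ(√(n/1641.6) × 10.98/√(1 − R²) − 1.960). R² is not in the documents, so a range is shown.

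| R² (assumed) | correlation | 123 per group | 150 per group |
|---|---|---|---|
| 0 | 0 | 85.2% | 91.3% |
| 4% | 0.20 | 86.6% | 92.3% |
| 9% | 0.30 | 88.3% | 93.6% |
| 25% | 0.50 | 93.4% | 96.9% |

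The gain is 1.0 to 5.6 points at 150 per group and 1.4 to 8.2 points at 123.

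**Step 4: check by simulation.** The crude test was compared with a logistic Wald test adjusted for one standard normal baseline covariate. The marginal risks were held at 43% and 25%, with 6,000 simulated trials per setting. The last column is the fall in variance of the standardised risk difference at 150 per group.

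| Odds ratio per SD (assumed) | 123: crude → adjusted | 150: crude → adjusted | variance cut |
|---|---|---|---|
| 1.35 | 85.2% → 85.6% | 91.2% → 92.0% | 1.7% |
| 1.65 | 85.3% → 86.6% | 91.3% → 92.6% | 4.8% |
| 2.46 | 85.3% → 89.2% | 91.3% → 94.5% | 12.5% |
| 3.67 | 85.5% → 92.6% | 91.5% → 96.5% | 22.5% |

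The simulation and the formula give the same picture.

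**Step 5: which end of the range.** Section 2.3.5 admits only patients with an ejection fraction above 50%, and section 2.3.6 excludes Killip class II or above and previous chronic HF. These limits truncate one proposed covariate directly and narrow baseline severity in general, so the lower rows are more plausible than the higher ones.

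**The case against.** The strongest reply is that nothing here is wrong. A chi-square or Fisher test of two randomised proportions is valid, it matches the sample size method, and its type I error already allows for chance baseline imbalance. All of that stands. A reader might infer that the unadjusted test is biased or invalid; the documents give no support for that.

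A second reply is that a condensed article leaves the primary model and its covariates to a fuller plan. That stands in part. The use of chi-square or Fisher as the primary HF test is inferred from the type of data. Even so, section 2.9 does commit to a test for count data, and the suggestion here is to replace that stated choice.

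A third reply is that the Cox model may already be the adjusted treatment comparison. A reader might infer the opposite, that it is purely a risk-factor analysis without a treatment term. Section 2.9 supports neither. Treatment is not excluded from the factors, and repeated recording of HF would suit such a model. All that can be said is that its covariates and role are undefined.

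Finally, power at 150 per group is about 91%, above the 85% target. The Discussion's remark about few cases might be read as a power shortfall, but the plan's own inputs do not show one. The margin does depend on analysing all 150 per group and on the full 18-point difference. As an assumed case, a test-group risk of 28% would give 77.9% power at 150 per group, and 82.0% if adjustment removed 10% of the variance.

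**Conclusion.** The point holds as a missed efficiency gain, small to moderate in size. On the natural reading, HF incidence is compared unadjusted while prognostic candidates measured before treatment go unused. Over an assumed R² of 4% to 25%, adjustment would lift power from about 91% to 92–97% at 150 per group, and from about 85% to 87–93% at 123 per group; the entry limits favour the lower end. This rests on three assumptions: that the chi-square or Fisher test is the primary HF comparison, that baseline BNP and ejection fraction predict HF in these patients, and that the planning risks of 25% and 43% hold. Validity is not in question, and the planned size already exceeds its power target, so the change is worthwhile but optional.

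**What to change.** Before unblinding, amend section 2.9 as follows.
- Make the primary comparison of HF incidence a logistic regression on treatment, with baseline log BNP, baseline ejection fraction and the randomisation strata as pre-specified covariates. Section 2.5 says that randomisation is stratified but does not name the factors, so they should be listed.
- Report the standardised (marginal) risk difference with its 95% confidence interval, which stays on the scale used for the sample size.
- Fill any missing baseline covariate by a rule that uses baseline data only, such as the overall mean, so that no patient is dropped for a missing covariate.
- Keep the chi-square or Fisher test as a supporting analysis.
- State that the Cox model is secondary, and list its covariates.

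The cost is wording and minor programming, with no new data, visits or patients. The one drawback is that the headline P value comes from a model rather than from a two-by-two table.
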